#### Plans to give access to the full protocol, participant level-data, and statistical code {31c}

This study protocol is registered with the registration number ISRCTN12746343 on the International Standard Randomized Controlled Trial (http://www.isrctn.com/ISRCTN12746343). The datasets analyzed during the current study are available from the corresponding author on reasonable request.

### Oversight and monitoring

#### Composition of the coordinating center and trial steering committee {5d}

There are several clinical study coordinators at each study center. Study coordinators play a role in coordination and study management. The trial steering committee (TSC) has an independent chair. In addition, the TSC has two public/patient group representatives, two clinical trials unit directors, statistician, and the principal investigator. If a member of the TSC withdraws during the course of the trial, we identify a replacement with a similar background. The members of TSC meet at the start of the trial and then weekly to review recruitment rates, protocol amendments, and any protocol deviations identified and may make recommendations to the sponsor regarding running the trial.

#### Composition of the data monitoring committee, its role, and reporting structure {21a}

The data monitoring committee is set up by the Beijing University of Chinese Medicine, and its members have no interest relationship with the sponsor. The members should have professional knowledge of medicine, pharmacy, health statistics, and be familiar with relevant laws and regulations of clinical trials. The committee monitors the eligibility, integrity, safety, and effectiveness of data in each research center through EDC system and question the problem data, which can be directly marked in EDC and generate a verification log. The modification traces of data by researchers in each center are also one of the monitoring contents. The data verification function of the EDC system is exclusive to the data monitoring committee, and the sponsor and researcher have no authority to carry out it. The committee also supervises protocol compliance, participant recruitment, and paper version clinical efficacy report every 2 weeks.

#### Adverse event reporting and harms {22}

Once an adverse event occurs, the investigator shall state to the subject that the subject is required to report truthfully the changes in his condition following the medication. Physicians are to avoid inducing questions.While observing efficacy, pay close attention to observing adverse events or unanticipated toxic side effects (including symptoms, signs, laboratory tests), analyze the causes, make judgment, and follow-up observations and records.For adverse events occurring during the study period, their symptoms, extent, time of appearance, duration, handling measures, experience, etc. should be recorded on a case report form, evaluated their relevance to the study drug, and recorded in detail by the investigator, signed, and dated.When an adverse event is identified, the observing physician may decide whether to discontinue observation based on the condition, and cases who discontinue because of adverse effects should be followed up with a detailed record of the handling and outcome.In the event of a serious adverse event in a study, the unit that assumes the responsibility for the clinical study must take immediate measures to protect the safety of subjects, must report to the project leader and the Research Center for clinical trials of drugs, should report within 24 h to the drug administration, the subject responsible unit, and the ethics committee. The investigator should also report to the data monitoring committee and relevant regulatory bodies as required indicating expectedness, seriousness, severity, and causality.Investigator should sign and date on report. The subject responsible unit will guarantee reporting procedures that meet all legal and regulatory requirements.When urgent breaking of blinding is required for a serious adverse event to occur in a clinical study, the blinding should be broken jointly by the project leader, investigator, clinical monitor.

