### Criteria for discontinuing or modifying allocated interventions {11b}

#### Shedding criteria

Cases that have been enrolled but do not complete the clinical protocol should be considered drop outs in the following circumstances:

1. Patients withdrew from the trial on their own;

2. Lost to follow-up;

3. Poor compliance;

4. Because some diseases are considered by the study physician to be amenable to withdrawal from the trial.

The case should be explained. If the baseline pharmacodynamic data are available, the results of the last major outcome can be transferred to the final result for statistical analysis, and the research records should be kept for reference.

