#### Procedure for unblinding if needed {17b}

At the end of the trial, the first-level uncovering blinding is performed after checking CRF, EDC, and signature. The groups of subjects are determined by the first-level uncovering blinding to conduct statistical analysis. After the statistics analysis, the second-level uncovering blinding is performed. Through the second-level blinding, the Xiaoyao pill group and the placebo group are determined to evaluate the drug efficacy. Unblinding is generally done at the end of the trial for statistical analysis and outcome assessment. However, in order to ensure the safety of the subjects, the blindness is uncovered in some emergency situations, such as the occurrence of a serious adverse event, unable to judge its relationship with the trial drug, whether it is overdosed, whether it has serious drug interactions with the concomitant medication, etc. When it is urgent, researchers need to know what drug to take to decide the rescue regimen. After uncovering blindness, it is necessary to record the time, reason for breaking the blindness in advance and the person performing the blind breaking, and to notify the inspector and the sponsor as soon as possible. Once the blindness is uncovered in advance, the participants should not continue to participate in the study. The data of these participants cannot be used for the efficacy evaluation analysis, but the data should still be included in the safety analysis data set. And the participants should be treated and protected in time. An emergency letter is prepared for every participant with an envelope made of thick, light tight paper. Unblinding of a single participant should not disrupt the blinding of the entire clinical trial. Emergency letters are made by a third-party person unrelated to this trial.

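### Emergency unblinding needs three roles acting jointly, a poor fit with its rescue purpose, and anyone unblinded early is barred from the efficacy analysis

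*Protocol article*

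**What the plan says.** **Who breaks the blind.** Protocol article, Adverse event reporting and harms {22}: when a serious adverse event calls for an urgent break, "the blinding should be broken jointly by the project leader, investigator, clinical monitor". The same section says that the responsible unit "must take immediate measures to protect the safety of subjects".

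Procedure for unblinding if needed {17b} covers emergency breaks as well. In the urgent case "researchers need to know what drug to take to decide the rescue regimen". "An emergency letter is prepared for every participant". The time, the reason and the person breaking the blind are recorded, and the site is to "notify the inspector and the sponsor as soon as possible". The section does not say who may open the letter.

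**What happens to the participant and the data.** Section {17b} continues: "Once the blindness is uncovered in advance, the participants should not continue to participate in the study". Then: "The data of these participants cannot be used for the efficacy evaluation analysis". The data stay in the safety set.

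**Related rules.**
- Shedding criteria (under {11b}): for a drop-out with baseline data, "the results of the last major outcome can be transferred to the final result for statistical analysis".
- Section {20c}: anyone with missing primary or secondary outcome data is excluded.
- Section {18b}: data of those who drop out or interrupt are analysed and explained separately.

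**The concern.** The two rules raise different problems.

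1. **Safety procedure.** An emergency letter is useful only if the doctor treating the participant can act on it. If three roles must take part, and the project leader or monitor cannot be reached, a rescue decision that depends on the drug may wait. A site reading {22} and {17b} together cannot tell whether its investigator may open the letter alone.

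2. **Efficacy comparison.** The reasons that {17b} gives for an early break include a serious adverse event, overdose and drug interaction. These occur after randomisation and may be related to treatment and to outcome. Removing such participants means that the groups compared are no longer those randomised. It also discards HAMD ratings obtained before anyone opened the letter.

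**Working it through.** **Part 1: the two sections side by side (no arithmetic applies).**

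| Point | {22} | {17b} |
|---|---|---|
| Trigger | Serious adverse event needing an urgent break | Emergencies, including a serious adverse event |
| Who acts | Project leader, investigator and monitor, jointly | A person who is recorded; role and number not fixed |
| Means | Not stated | One letter per participant |
| Others | Parties to the break | Inspector and sponsor are notified |

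The sections overlap for a serious adverse event. If the inspector in {17b} is the monitor in {22} (an assumption; the text does not define the term), one section informs a person whom the other makes a party to the break. That is a poor fit. It is not a logical conflict, because {17b} leaves open who opens the letter.

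**Part 2: what the bar discards.** Section {12} plans four HAMD assessments: baseline and weeks 1, 2 and 4. Ratings already made when the blind is broken:
- after the week 1 visit: 2 of 4;
- after the week 2 visit: 3 of 4;
- after the week 4 visit: 4 of 4.

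**Overlap with {20c}.** Participation ends at the break, so a participant unblinded before week 4 has no week 4 score and is excluded under {20c} anyway. The bar acts alone only where no outcome is missing. Deleting it without changing {20c} would therefore rescue few participants.

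**Part 2: size.** Inputs from Sample size {14}: 30 required per arm, 15% dropout, 72 patients recruited, rates 91.4% and 32.7%.

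- The plan's own figure: 30 / (1 - 0.15) = 35.3, rounded up to 36 per arm, or 72. It reproduces.
- One break removes 1/36 = 2.8% of an arm, and 1 of the 36 - 30 = 6 places above the required number.
- Planning counts: 0.914 × 36 = 32.9, about 33/36 = 91.7%; 0.327 × 36 = 11.8, about 12/36 = 33.3%. Difference: 58.3 points.

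The number of breaks is not given. One or two removals from one arm are assumed; where two, both have the same response status.

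| Removed | One: new rate | Change in difference | Two: new rate | Change in difference |
|---|---|---|---|---|
| Xiaoyao non-responder | 33/35 = 94.3% | +2.6 | 33/34 = 97.1% | +5.4 |
| Xiaoyao responder | 32/35 = 91.4% | -0.2 | 31/34 = 91.2% | -0.5 |
| Placebo non-responder | 12/35 = 34.3% | -1.0 | 12/34 = 35.3% | -2.0 |
| Placebo responder | 11/35 = 31.4% | +1.9 | 10/34 = 29.4% | +3.9 |

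These are changes in response rates. The effect on the HAMD score compared by ANCOVA in {20a} cannot be computed, because the document gives no HAMD mean or standard deviation.

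**The case against.** **On the joint break.** A reader might infer that {22} and {17b} contradict each other, or that treatment must wait for three signatures. The documents support neither. Section {17b} names no role for opening the letter, an operational detail that an article may leave to the full protocol. Agreement by telephone is not ruled out. The joint break is worded as something that should happen, whereas immediate protection of the participant is mandatory. The comparator is a starch and maltose placebo, so a clinician can often treat as though the active product was taken. What stands is that the three-role rule is itself stated, for exactly the urgent case, and {17b} recognises that knowing the drug can matter for rescue.

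**On the efficacy bar.** A reader might infer that these data vanish, or that the result is materially biased in favour of Xiaoyao pills. Neither follows. The data remain in the safety set, and {18b} may have them reported separately if it covers these participants. Breaks are probably few, since severe suicidal risk and severe primary disease are exclusions. The shift can go either way. Precision is not the issue: the stated rates need only 13 per arm at 90% power (16 with continuity correction) against 30 planned, and the 15% allowance exists to absorb losses.

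Nor does the drop-out rule clearly rescue these data. It is permissive, its listed circumstances do not name unblinding, and {20c} pulls the other way. The overlap with {20c} also stands: most of the loss before week 4 would occur without the bar.

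One caveat concerns the ratings themselves. Section {17a} says that outcome assessors do not take part in the blinding, which is unclear. Pre-break ratings can be called ratings made before that participant's letter was opened; whether every assessor was blind then is not settled by the text.

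What remains is a stated exclusion triggered by events that may depend on treatment. Neither safety-set retention nor separate reporting restores the randomised comparison.

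**Conclusion.** Both points hold in limited form, and both rules should be changed.

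1. The joint rule fits poorly with the rescue purpose of emergency unblinding and could delay a choice that depends on the drug. The exposure is confined to that choice. The delay cannot be quantified, and it rests on the assumption that the three roles are not always reachable together.

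2. The efficacy bar is a post-randomisation exclusion that may depend on treatment, and it discards up to all four HAMD ratings for the participant concerned. At the planning rates, one removal shifts the 58.3-point difference by -1.0 to +2.6 points, and two from one arm by -2.0 to +5.4. With few breaks, the likely effect is small against the planned contrast and its direction is not known in advance. The reason to change the rule is that it is wrong in principle and cheap to correct, not that it threatens the trial's conclusion.

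**What to change.** **Sections {22} and {17b}, breaking the blind.** State that the treating investigator may open that participant's emergency letter alone when rescue treatment requires it. The investigator records the time, the reason and who opened it, then promptly notifies the project leader, monitor and sponsor, without disclosing the allocation unless they need it.

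**Section {17b}, efficacy.** Delete the bar. Analyse these participants in the group to which they were randomised, using the HAMD ratings made before the break.

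**Section {20c}.** State that a missing week 4 does not exclude them. Either impute week 4 by multiple imputation from the available baseline, week 1 and week 2 scores before the planned ANCOVA, or use a repeated-measures model. Single imputation should be avoided because it understates uncertainty.

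**Later visits (optional).** If scheduled HAMD visits are kept after study drug stops and the participant agrees, flag ratings made after the break and use them only in a sensitivity analysis, since they are no longer blind. At most three scheduled visits (weeks 1, 2 and 4) are involved.

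**Cost.** A wording amendment with ethics approval and written participant consent under {25}, a notice to the five sites, and a little more analysis work. It needs no extra patients and no new visit types. The article describes the trial as still recruiting, so on the document the change can still take effect.

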#### Frequency and plans for auditing trial conduct {23}

The sponsor and the study center meet weekly to ensure that the study is being conducted in accordance with the study protocol.

#### Plans for communicating important protocol amendments to relevant parties (e.g., trial participants, ethical committees) {25}

If the study protocol is amended, it must be approved by the ethics committee of the Beijing University of Chinese Medicine, and patients are also provided written informed consent to inform the modification. Sponsor and funder are notified first. Then, the principle investigator notifies the centers and a copy of the revised protocol is sent to the principle investigator to add to the Investigator Site File. Any deviations from the protocol are fully documented using a breach report form. The protocol also is updated in the clinical trial registry.

#### Dissemination plans {31a}

The results of this study will be published in a scientific journal.

## Discussion

Depression is a common affective mental disorder, which is associated with a high burden of disease. Research suggests that chronic diseases, genetic factors, social, and environmental factors can induce depression [22]. The common therapy for depression is antidepressants. Due to the side effects of drugs for depression, the compliance of patients is rather poor and then affect the drug efficacy [23]. Therefore, it is urgent to find safe and no side-effect treatment. A number of patients with depression would prefer traditional Chinese medicine over pharmacotherapy when our study demonstrates the effectiveness and safety of traditional Chinese medicine to treat depression. This will be especially relevant for patients who do not respond to medical therapy or who experience adverse side effects to drug therapy.

According to traditional Chinese medicine theory, liver stagnation and spleen deficiency syndrome is one of the main syndromes of depression. Especially due to people’s unhealthy eating habits and long-term emotional stress from life and work in modern society, the symptoms of the liver stagnation and spleen deficiency are very common. In clinical practice, the syndrome of liver stagnation and spleen deficiency has become a high incidence and common syndrome. Xiaoyao pills has good effect of soothing the stagnated liver and strengthening the spleen. In our study, TCM syndrome efficacy evaluation is added in order to determine more suitable patient populations to take Xiaoyao pills and optimize indications.

The potential mechanism of Xiaoyao pills to treat depression mainly focused on animal experiments [24–28]. There is little evidence about the potential mechanism about Xiaoyao pills to treat depression in clinical studies. Therefore, in addition to the efficacy evaluation of Xiaoyao pills, the action mechanism of Xiaoyao pills from the perspective of transcriptomics and DNA methylation sequencing will also be studied in our trial.

However, our study has limitation. The limitation concerns the fact that we will only recruit mild to moderate depression patients with syndrome of liver stagnation and spleen deficiency in order to ensure the curative effect. Effectiveness of TCM for different types of depression is not evaluated.

Therefore, a clinical trial about traditional Chinese medicine to treat different types of depression are still needed.

### Trial status

The trial is currently in the recruitment phase. *This study protocol is version 3 made on June 1, 2020. Recruitment commenced in March 2020 at Peking University Sixth Hospital and is expected to be completed in December 2021.*

## Abbreviations

DSM-5: Diagnostic Statistics Manual of Mental Disorders
HAMD: Hamilton Depression Scale
TCM: Traditional Chinese medicine
LC-M: Liquid chromatograph-mass spectrometer
GO: Gene ontology
KEGG: Kyoto Encyclopedia of Genes and Genomes
AEs: Adverse events
CRF: Case report forms
CRC: Clinical research coordinator
TSC: Trial Steering Committee (TSC)
ANCOVA: Analysis of covariance
EDC: Electronic data capture
